## Abstract

**Background:**

Several randomized controlled trials have compared different suture materials and techniques for abdominal wall closure with respect to the incidence of incisional hernias after midline laparotomy and shown that it remains, irrespective of the methods used, considerably high, ranging from 9% to 20%. The development of improved suture materials which would reduce postoperative complications may help to lower its frequency.

**Design:**

This is a historically controlled, single-arm, multi-centre, prospective trial to evaluate the safety of MonoMax^® ^suture material for abdominal wall closure in 150 patients with primary elective midline incisions. INSECT patients who underwent abdominal closure using Monoplus^® ^and PDS^® ^will serve as historical control group. The incidences of wound infections and of burst abdomen are defined as composite primary endpoints. Secondary endpoints are the frequency of incisional hernias within one year after operation and safety. To ensure adequate comparability in surgical performance and recruitment, the 4 largest centres of the INSECT-Trial will participate. After hospital discharge, the investigators will examine the enrolled patients again at 30 days and at 12 ± 1 months after surgery.

**Conclusion:**

This historically controlled, single-arm, multi-centre, prospective ISSAAC trial aims to assess whether the use of an ultra-long-lasting absorbable monofilament suture material is safe and efficient.

**Trial registration:**

NCT005725079

## Background

Midline laparotomy is a standard method for gaining access to the abdominal cavity. However, in spite of a great number of different suture materials and techniques being available to achieve closure of the abdominal wall, the incidence of abdominal wall hernia remains high (ranging from 9% to 20%) [1-3]. The latest data show that 52% of incisional hernias occur within 6 months postoperatively, 68% within one year and 79% within two years after surgery [3,4]. They do not only require most often surgery, but even after adequate treatment, they show recurrence rates up to 45% [5]. Another complication of a complex abdominal wall closure is a burst abdomen occurring in 1% to 3% of the patients within the first days after laparotomy [6-8].

### Rationale

Various randomized controlled trials and four corresponding meta-analyses reported in the literature have compared different suture – slowly absorbable versus rapidly or non-absorbable – materials or different suture – interrupted versus continuous running – techniques for abdominal wall closure [9-14]. These studies suggest that, using a running suture technique, slowly absorbable monofilament sutures may be the best choice for abdominal wall closure. As one possible reason for the still relevant incidence of incisional hernias, experimental research has demonstrated that, one year after a midline laparotomy, the abdominal fascia retains only 70% of its original strength, suggesting that adequate abdominal wall closure preferably needs a longer-lasting supporting suture [4]. Even though synthetic absorbable sutures such as polyglactin, polyglycolic and polydioxanone are slowly absorbable, they are fully absorbed after 70 to 180 days. Therefore, an ultra-long-term absorbable suture material may help to reduce the above mentioned postoperative complications such as incisional hernia or burst abdomen.

### Purpose

The ISSAAC-Trial, a prospective multi-centre historically controlled trial, was designed to evaluate the clinical safety and efficacy of MonoMax^®^, a new suture material. MonoMax^® ^is an ultra-long-lasting, absorbable, flexible and elastic monofilament with superior initial strength and predictable constant degradation rate. Compared to other absorbable monofilament suture materials, MonoMax^® ^shows superiority in knot and long-lasting linear tensile strength retention and provides additional security, indicating that MonoMax^® ^might be very well suitable for abdominal wall closure. To ensure optimal comparability with the study population of the INSECT-Trial as well as fast patient recruitment, only the four centres most successful in recruiting patients for the INSECT-Trial will enrol patients for the ISSAAC-Trial.

## Methods/Design

### Study objectives

The aim of the ISSAAC-Trial is to show the safety and efficacy of MonoMax^® ^suture material. To assess its safety, parameters such as wound infections and re-operation due to burst abdomen will be evaluated. It is expected that the frequency of both parameters may be equal or lower in the ISSAAC patient cohort than in the INSECT patient cohort. To assess its efficacy, the frequency of abdominal hernias at 12 ± 1 months after surgery is taken as parameter and is also expected to may be equal or lower than in the INSECT-Trial [15,16].

The hypothesis would be that that the frequency of wound infection and of re-operation due to burst abdomen until day of discharge are equal or lower in the patient cohort enrolled in the ISSAAC-Trial compared to patients included in the INSECT-Trial.

For the ISSAAC-Trial, a standardized surgical technique of abdominal wall closure with continuous monofilament sutures is being used as it was in the INSECT-Trial. Thus, the results obtained from both trials will be comparable. To this end, only patients operated with the use of either MonoPlus^® ^or PDS^® ^as suture material during the INSECT-Trial will be included in the control group, excluding the patients randomized to interrupted sutures.

The composite primary endpoints of the ISSAAC-Trial are the frequency of wound infection, defined as redness, wound dehiscence with secretion (putrid or caliginous, smelly fluid) and/or microbiologic evidence of bacterial contamination, and the frequency of re-operation due to burst abdomen until day of discharge (see Table 1).

**Table 1 T1:** Definition of complications

Complication	Definition
Burst abdomen	Postoperatively missing continuity of the abdominal fascia in combination with a wound dehiscence and consecutive relapse operation.
Wound infection	Redness, wound dehiscence with secretion either of putrid or caliginous, smelly fluid and/or mircobiologic evidence of bacterial contamination.
Incisional hernia	A hernia is present if the ultrasound shows a fascial gap and a protruding hernial sac and the clinical exam is consistent with a hernia.
Complicated wound healing	Incision has not completely closed. Necrosis of the wound edge or primary or secondary dehiscence occurs. Formation of seroma, fistula, necrosis, and bleeding.

The secondary endpoints of the ISSAAC-Trial are the frequency of abdominal hernias at 12 ± 1 months after surgery, the frequency of wound-infection and complicated wound healing at 30 days after surgery, and the length of the hospital stay.

The incidence of incisional hernia within 12 ± 1 months after the operation diagnosed by physical and ultrasound examination is considered as secondary endpoint. A hernia is deemed present if the ultrasound examination shows a fascial gap and a protruding sac and if confirmed by the clinical examination. Assessment and documentation will be performed by a person who is familiar with the examination of the abdominal wall, but not involved in the surgical procedure. The ultrasound examination will be carried out by an investigator who has at least 6 months training in this method.

### Ethics and informed consent

The final protocol was approved by the Ethics Committee of the University of Heidelberg Medical School. Secondary approval was obtained from all local ethics committees responsible for the participating centres. All patients eligible will be asked whether they are willing to participate in the trial and informed about the purpose of the trial, the operative procedures as well as their options and risks. Written informed consent will be obtained from all patients participating in the trial.

### Intervention

#### Surgical technique

The operation begins with a skin incision performed with the electric cautery which penetrates through the subcutaneous layer. Next, the abdominal fascia is separated in the midline line with the electric cautery. Then, the incision of the peritoneum is made with the scissors and completed with the electric cautery. The surgical procedure is carried out in the usual fashion and according to local standards regarding the indication for the intervention.

Starting either from the cranial end or from the caudal end of the wound, the abdominal wall is closed by placing four Mikulicz or equivalent clamps at the edges of the abdominal fascia and a continuous all-layer suture using two MonoMax^® ^loops (USP1/Aesculap AG, Tuttlingen, Germany). Before use, in order to avoid breakage of the material, the monofilament suture MonoMax^® ^has to be stretched once by the assisting nurse/operation technician. The first stitch should be anchored cranially and caudally of the incision. The distance to the edge of the fascia and the distance between two stitches should not exceed 2 cm to 2.5 cm. After having closed half of the wound, the surgeon cuts one end of the loop immediately below the needle, passes it then from the opposite edge of the fascia and ties both ends with at least four knots. He proceeds in the same manner with the loop from the caudal end of the wound which intersects the other loop at the middle of the incision, both sutures lines overlapping at least 2 cm. For every patient two loops must be used, irrespective of the length of the wound. After completion of the fascia closure, the loop is cut directly underneath the needle.

No subcutaneous or drainage is inserted. The skin is closed with skin clips or interrupted sutures with monofilament non-absorbable sutures. At the end of the intervention, the length of the incision is measured in cm.

During the first investigator meeting (November 22^th^, 2007, Stuttgart, Germany), all participating trial centres were retrained in the required technique using abdominal wall models of mini-pigs and provided with a CD-ROM demonstrating the required surgical technique. Furthermore, they have continuous access to technical support by suture product specialists from Aesculap AG for all suture-related issues and questions.

#### Postoperative intervention

After discharge from the hospital, the investigators will examine the patients at 30 days and at 12 ± 1 months after surgery. All complications leading to re-operation due to burst abdomen, wound infection and complicated wound healing will be documented within 30 days after surgery. At one year postoperatively, the incidence of incisional hernias will be recorded by physical and abdominal ultrasound examination. In total, the trial will last 12 ± 1 months for each patient (see Table 2).

**Table 2 T2:** Flow Chart ISSAAC Trial

	Visit 1 (Screening)	Visit 2 (day 0)	Visit 3 (day 2 ± 1)	Visit 4 (day of discharge or the day before)	Visit 5 (day 30 ± 5)	Visit 6 (12 ± 1 months post surgery)
Informed consent	X					
Demographic data*	X					
BMI	X					
Smoker/non-smoker	X					
Inclusion/exclusion	X					
Medical history	X					
Physical examination	X		X1)	X1)	X1)	X2)
Reason for surgery	X					
Surgery		X				
Board certified surgeon		X				
Deviations from surgical procedure as described in protocol		X				
Ultrasound of the abdominal wall						X
Abdominal Adverse Event/Serious Adverse Event		X	X	X	X	X
Re-operation due to burst abdomen necessary?			X	X	X	X
Wound infection			X	X	X	
discharge				X		

1) of the abdomen and the laparotomy wound

2) of the abdomen

* date of birth, gender, weight, height

### Clinical sites

The selected sites were most successful in enrolling patients for the INSECT-Trial. Therefore four centres located in Germany will recruit 150 patients (for all inclusion and exclusion criteria see Table 3). All investigators are hospital-based general surgeons.

**Table 3 T3:** Eligibility Criteria

Inclusion criteria	Exclusion criteria
Age equal or greater than 18 years	Peritonitis
Expected survival time more than 12 months	Emergency surgery
Patients undergoing primary and elective midline laparotomy (patients with prior laparoscopy or abdominal operation via paramedian incision (e.g. appendectomy) may be included in the trial	Coagulopathy (= A group of disorders of the blood clotting (coagulation) system in which bleeding is prolonged and excessive with abnormal values in the blood laboratory • Lack of compliance
BMI < 35	Severe psychiatric or neurologic disease
Expected length of skin incision > 15 cm	Lack of informed consent
	Participation in another intervention with interference of intervention and outcome of this trial
	Drug- and/or alcohol-abuse according to local standard
	Current immunosuppressive therapy (more than 40 mg of a corticoid per days or azathioprin
	Chemotherapy within two 2 before operation
	Radiotherapy of the abdomen completed less than 8 weeks before operation
	Inability to understand and to follow the instructions given by the investigator (e.g. insufficient command of language, dementia, lack of time)
	Pregnant or breast-feeding woman (according to information given by the patient)
	Patients who have been committed to an institution by virtue of an order issued either by the courts or by an authority

### Safety aspects

The term "adverse event" covers any sign, symptom, syndrome, illness that appear or worsen in a subject during the period of observation in the clinical trial and that may impair the well-being of the subject. The term also covers laboratory findings of other diagnostic procedures that are considered to be clinically relevant.

A "serious adverse event" is any adverse event occurring at any time during the period of observation that results in death, is immediately life-threatening, requires or prolongs hospitalization, results in persistent or significant disability or incapacity.

All adverse events occurring in the abdominal region between the beginning of wound closure and the last visit of the patient at 12 months postoperatively must be documented on the appropriate AE form in the CRF, excluding adverse events that affect other body systems as they are not related to the intervention. Complications such as burst abdomen, wound infection, complicated wound healing, presence of incisional hernia are defined as adverse events (for definition see Table 1). Re-operation due to burst abdomen is classified as a serious adverse event.

Analysis of safety related data performed with respect to:

- Frequency of SAEs

- Frequency of SAEs stratified by severity

- Frequency of SAEs stratified by causality.

The sponsor will notify the competent authorities, ethics committees and all investigators concerned of unexpected SAEs and unexpected adverse device effects in line with applicable regulatory requirements.

As the adverse event definition used in the INSECT-Trial was broader, two surgeons will independently select from this trial's list of adverse events the adverse events to be taken for comparison in the present trial in accordance with the established definition.

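### Safety aspects rules out relatedness in advance for all non-abdominal events, against its own SAE provisions, and filters adverse events differently in ISSAAC and INSECT

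*Protocol article*

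**What the plan says.** All of the following is in the protocol article, section Safety aspects, unless another place is named.

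- The general definition is broad: "The term 'adverse event' covers any sign, symptom, syndrome, illness that appear or worsen in a subject during the period of observation". A serious adverse event is any such event with a serious outcome, death included. Neither definition names a body system.
- Recording in ISSAAC is narrower. What must go on the AE form is "All adverse events occurring in the abdominal region between the beginning of wound closure and the last visit of the patient at 12 months postoperatively". The reason for leaving out the rest stands in the clause "excluding adverse events that affect other body systems as they are not related to the intervention".
- The planned safety analysis covers SAEs overall, by severity and by causality ("Frequency of SAEs stratified by causality"). The sponsor must also notify unexpected SAEs and unexpected adverse device effects.
- For the comparator: "As the adverse event definition used in the INSECT-Trial was broader, two surgeons will independently select" the events to compare. They draw on the INSECT event list, and the only criterion given is that the choice be made "in accordance with the established definition".
- The abstract describes the comparator as non-concurrent: "INSECT patients who underwent abdominal closure using Monoplus^® ^and PDS^® ^will serve as historical control group".
- In Table 2 (Postoperative intervention) the only adverse event row is an abdominal AE/SAE row. It is unclear whether the word abdominal limits the serious events as well.

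**The concern.** There are two separate problems.

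**Relatedness is fixed before any event is seen.** Whether an event is related to the suture is what a causality assessment should decide. Here it serves as the reason for not recording the event. Safety is a stated aim of the trial (Study objectives), and the material is described as new (Purpose). A systemic effect that nobody expected is the kind of event that the notification duty exists for, and the recording rule could leave it out.

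**The two adverse event lists are produced by different processes.** In ISSAAC, a site investigator decides at the bedside whether an event is abdominal and needs a form. In INSECT, events were recorded under a wider definition and are reduced afterwards by two surgeons reading a list. A borderline event therefore meets a different filter depending on the trial it occurred in. With a historical control and no randomisation, a difference in filters cannot be told apart from a difference between sutures.

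**Working it through.** The document gives no adverse event rate and no error rate for the selection, so there is no planned figure to reproduce. The check sets the text side by side.

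**Part 1: the recording rule against the rest of the section**

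1. An SAE is defined as an adverse event with a serious outcome, so SAEs are a subset of AEs.
2. The recording rule excludes AEs of other body systems. No exception is made for serious ones, so by step 1 the exclusion reaches them too.
3. The SAE analysis by causality then runs on a set already filtered by presumed causality. A non-abdominal SAE cannot appear in any causality category because it was never entered.
4. Notification of an unexpected device effect needs someone to have recorded the event and judged it. The rule removes the recording step for every non-abdominal event.
5. Table 2 does not settle the matter. If abdominal qualifies both AE and SAE, it repeats the exclusion. If it qualifies AE only, it contradicts the text.

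**Part 2: the two routes to the compared list**

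- *Scope intended:* the same in both trials, since the INSECT selection follows the ISSAAC definition.
- *Who filters:* site investigators in ISSAAC; two surgeons, independently, for INSECT.
- *When:* at the time of recording in ISSAAC; after recording in INSECT.
- *From what:* events as they occur in the patient in ISSAAC; a finished list recorded under a broader definition in INSECT.
- *Masking:* none stated for either.

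The definition is aligned and the process is not. If the surgeons keep borderline events that an ISSAAC investigator would not have recorded, the control rate is too high and ISSAAC looks better. If they are stricter than the investigators, the bias runs the other way. Nothing in the document says which is more likely.

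**Part 3: what depends on this**

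Statistical considerations sets the significance test of the ISSAAC event rate against a fixed 25%. The INSECT selection does not enter that test. It enters the adverse event comparison with INSECT.

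**The case against.** The selection step was written to remove an inequality. INSECT used a broader definition, so an unfiltered comparison would be worse. The step is done in duplicate, independently, and tied to the ISSAAC definition. This stands: the intended scope is equal, and only the process differs.

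Masking and the handling of disagreements are details that an article may leave to the full protocol. This also stands in part. The absence of a disagreement rule is not held against the plan here. What remains is what the text does state, namely that the later selection is made from the INSECT list.

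A reader might infer that the surgeons know they are handling the control arm and that each event they keep raises the control rate. The document does not say this. They probably know that the list comes from INSECT, but INSECT also had an interrupted-suture arm that is excluded from the control group, and masking to suture is neither stated nor ruled out.

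A reader might also infer that deaths and systemic effects cannot be found in ISSAAC. That goes too far. The SAE definition covers death, notification of unexpected events is required, the trial is run under the medical device law and GCP (Trial organization, coordination and registration), and the abdominal limit is worded for the AE form. The text pulls in two directions. It shows that such events could go unrecorded, not that they would.

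**Conclusion.** The point holds in two parts.

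1. The advance declaration that non-abdominal events are unrelated conflicts with the SAE definition, the causality analysis and the notification duty in the same section. It is a stated rule with a stated reason, so it is not a detail left to a fuller document.
2. Adverse event ascertainment is asymmetric. ISSAAC is restricted at source, and INSECT is selected afterwards, on the control side only and without stated masking.

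The second part bears on the adverse event comparison with INSECT. It would be a mistake to read it as undermining the primary analysis. The test against 25% does not use the selected list, and wound infection and burst abdomen have their own definitions in Table 1 and their own rows in Table 2. The direction and size of any bias are unknown, and a figure would have to rest on invented rates, so none is given. The change should be made, but it does not invalidate the design.

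**What to change.** 1. **Recording.** Record every SAE and every death in ISSAAC whatever the body system, and assess causality for each. Keep the abdominal restriction for non-serious AEs only. Delete the statement that events in other body systems are unrelated, and word the Table 2 row to match. *Cost:* additional SAE forms over 12 months in 150 patients. The number cannot be stated from the document, and after laparotomy it may not be trivial, because any hospitalisation counts.

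2. **Selection.** First remove the clearly non-abdominal, non-serious INSECT events by body system. ISSAAC would have no such entries, so leaving them in would reveal the trial. Then have the two surgeons apply the ISSAAC definition to one pooled listing from both trials, with trial, suture and dates masked, before any rates are tabulated. Report the comparison twice: counting an event if either surgeon selects it, and counting it only if both do. *Cost:* preparing the masked listing and the surgeons' time for the ISSAAC entries. The surgeons are already planned.

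The pooled review makes the selection common to both trials. It cannot recover borderline non-serious events that an ISSAAC investigator never entered, and the report should say so.

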### Statistical considerations and sample size estimation

Patients are included for primary analysis if information about complications is available up to the day of discharge. Non-compliant and compliant patients will be compared with respect to age and sex distribution.

About 80 patients from the INSECT-Trial will serve as control group. Using the 1:4 rule, up to 320 patients could be collected in a sensible manner. Within a reasonable time-frame of 1 year, 150 patients could be enrolled into the ISSAAC-Trial. Assuming a drop-out rate of 7%, 140 patients could be subjected to an analysis with respect to the primary endpoints. This would be sufficient to construct a 90% confidence interval around the estimate that would not cover the value of 25% with a power of 10% when the true event rate is at 15%.

It is expected that the historical control group will comprise about 130 patients who had been enrolled into the INSECT-Trial. To make the comparison with the historical control group as meaningful as possible (using an "information per patient" metric), the size of the MonoMax^® ^group should not exceed the size of the control group by too much und has been accordingly established at 150 patients, allowing for 10 drop-outs.

Each participating centre should add at least 1/4 to the patients it had recruited during the INSECT-Trial, e.g. Marburg at least 7 patients and the other three at least 10 patients each. In order to avoid a centre effect, no participating hospital should include more than 80 patients.

The level of significance for the confidence intervals is set at 95 and 90% in order to perform a one-sided test of significance against the 25% event rate stated in the null hypothesis.

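### The entry rule for the primary analysis, read literally, can exclude patients with a recorded event who die or withdraw before discharge, risking informative exclusion in the single-arm test against 25%

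*Protocol article*

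**What the plan says.** Under Statistical considerations and sample size estimation, the protocol article sets the rule for entering the primary analysis: "Patients are included for primary analysis if information about complications is available up to the day of discharge". The same section gives the expected loss, "Assuming a drop-out rate of 7%, 140 patients could be subjected to an analysis with respect to the primary endpoints", and says that the group size "has been accordingly established at 150 patients, allowing for 10 drop-outs". It does not say what those drop-outs are.

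The endpoint window closes at discharge. Study objectives names wound infection and "the frequency of re-operation due to burst abdomen until day of discharge". Table 2 places the in-hospital assessments at day 2 ± 1 and at discharge or the day before.

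Two further statements bear on the point. On patients who do not comply, the statistical section says: "Non-compliant and compliant patients will be compared with respect to age and sex distribution". Under Safety aspects, abdominal adverse events from the start of wound closure "must be documented on the appropriate AE form in the CRF", and wound infection and burst abdomen are among them.

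**The concern.** Entry to the analysis depends on whether outcome information is complete, which is settled after the operation and may be related to the outcome. The condition runs to discharge. It does not run to the first event or discharge, whichever comes first. Taken at its word, a patient whose wound infection is recorded on day 5 and who withdraws on day 8 does not meet it, and a patient who dies in hospital has no day of discharge. The adverse event form would hold the event while the primary numerator might not.

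The primary result is one proportion compared with a fixed 25%, so nothing in the design cancels a selective loss. If the excluded patients have more events than the rest, the estimate favours the new suture and the chance of a false safety conclusion rises. An age and sex comparison cannot reveal this, because it does not look at event status.

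**Working it through.** **Inputs from the article (Statistical considerations and sample size estimation).** Enrolled 150; drop-out 7%; analysed 140; null rate 25%; assumed true rate 15%. On confidence level: "The level of significance for the confidence intervals is set at 95 and 90% in order to perform a one-sided test of significance". I use the 90% two-sided interval, which corresponds to a one-sided 5% test.

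**Input not in the article.** The event rate q among excluded patients. I show the range from 0 to 1.

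**1. The plan's own figures.**
- 150 × (1 − 0.07) = 139.5, so 140 analysed and about 10 lost. This reproduces.
- With n = 140, the exact (Clopper-Pearson) 90% upper limit is below 25% for at most 26 events: 26/140 gives 24.8%, 27/140 gives 25.6%. The Wilson interval has the same cut-off.
- The chance of 26 or fewer events is 90.1% at a true rate of 15% and 4.5% at 25%. The article's phrase is "not cover the value of 25% with a power of 10% when the true event rate is at 15" percent. The 10% there matches the type II error, not the power. That is a separate matter, but it confirms that 26 of 140 is a sensible reading of the decision rule.

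**2. Effect on the estimated rate.** If the true rate in all 150 is p and the 10 excluded patients have rate q, the rate among those analysed is (150p − 10q)/140. For p = 15%:

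| q | Rate analysed | Shift (points) |
|---|---|---|
| 0 | 22.5/140 = 16.1% | +1.1 |
| 0.15 | 21/140 = 15.0% | 0 |
| 0.5 | 17.5/140 = 12.5% | −2.5 |
| 1 | 12.5/140 = 8.9% | −6.1 |

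**3. Effect on the false-pass chance.** Same formula with p = 25%, then the binomial probability of at most 26 events in 140:

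| q | Rate analysed | Chance of wrongly ruling out 25% |
|---|---|---|
| 0 | 37.5/140 = 26.8% | 1.5% |
| 0.25 | 35/140 = 25.0% | 4.5% |
| 0.5 | 32.5/140 = 23.2% | 11.3% |
| 1 | 27.5/140 = 19.6% | 42.4% |

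**4. Excluded events needed to reverse a pass.** Add k excluded events to the numerator, use 150 as denominator, and treat the other 10 − k patients as event-free. With 150 patients, 28 events pass (18.7%, upper limit 24.7%) and 29 fail (19.3%, upper limit 25.4%). So k = 29 − observed events:
- 21/140 (15.0%, upper limit 20.9%): k = 8
- 24/140 (17.1%, upper limit 23.3%): k = 5
- 26/140 (18.6%, upper limit 24.8%): k = 3

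For 21/140, the best case is 21/150 (14.0%, upper limit 19.5%) and the worst case is 31/150 (20.7%, upper limit 26.9%).

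**The case against.** The article nowhere says that a patient with a known event is removed. Someone with a recorded wound infection arguably has the complication information that the rule asks for, and the adverse event rules mean that it would be on file. This stands: exclusion is the literal reading, not a stated intention.

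A reader might also infer that the rate will be biased downward. The documents do not support that. Leaving out event-free deaths or withdrawals moves the rate up, equal rates leave it unchanged, and no figure is given for events among patients lost before discharge.

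A reader might infer that the plan expects 10 patients to be lost through this rule. It does not say so. The 10 are a sample-size allowance without a cause. Consent precedes surgery in Table 2, so some may never be operated on or never be closed with MonoMax, and no sensible analysis set would include those.

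Early discharge is not a loss either, because the endpoint ends at discharge. The exposed cases are mainly in-hospital death and withdrawal before discharge, in elective patients with an expected survival above 12 months.

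Finally, a reversal takes many events among few patients: 8 of 10 at the planned rate, 5 of 10 at 24/140. If excluded patients had the planned 15% rate, 5 or more events in 10 would have a probability of about 1%.

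These points limit the direction and size. They do not remove the defect. The sentence is a stated rule for the primary analysis set, not a detail left to another document, and it is unclear for the patients whose classification matters most.

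**Conclusion.** The concern holds as a risk of informative exclusion created by a badly fixed rule. It does not hold as a demonstrated downward bias. The literal wording can remove patients with a recorded primary event who die or withdraw before discharge, and the test against 25% has no concurrent arm to absorb that.

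The false-pass chance runs from 1.5% to 42.4%, against 4.5% when excluded and analysed patients have the same rate. This range assumes that all 10 allowed drop-outs are excluded after surgery, a true rate of 25%, and an exact 90% interval. Fewer post-operative exclusions would narrow it. The bias favours the suture only if excluded patients have the higher event rate. Close to the pass boundary, three excluded events are enough to change the conclusion.

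**What to change.** Define the primary analysis set as all enrolled patients whose fascia was closed with MonoMax. Count as an event any wound infection or re-operation for burst abdomen recorded before discharge, death or withdrawal, however long the patient was observed. For patients whose status remains unknown, report the result twice, with all of them event-free and with all of them as events. Apply the same rule to the INSECT controls as far as their data allow.

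The cost is a change of wording and one extra table. The estimate may turn out slightly less favourable to the suture.
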